## Abstract

**Background:**

Stroke is a health problem with serious consequences, both in terms of mortality, and after-effects affecting patient quality of life. Stroke requires both urgent and chronic management involving the entire health care system. Although large variability in the management of stroke patients have been noticed, knowledge of the diversity and the scalability of post-stroke pathways, whether it is the care pathway or the life pathway, is currently not sufficient. Moreover the link between post-stroke pathways and patients sequelae have not been yet clearly defined. All this information would be useful to better target the needs to improve stroke patient management.

The purposes are to identify the post-stroke life pathways components associated with sequelae (activity limitations – main purpose, cognitive disorders, anxio-depressive disorders, fatigue, participation restrictions) at 3 months and 1 year post-stroke, to define a typology of life pathways of patients during the post-stroke year and to analyze the social and geographical inequalities in the management of stroke.

**Methods:**

Design: a prospective multicenter comparative cohort study with a follow up to 1 year after the acute episode.

Participant centers: 13 hospitals in the Aquitaine region (France).

Study population: patients diagnosed with a confirmed ischemic or hemorrhagic stroke included in the Aquitaine Observatory of Stroke (ObA2) cohort and voluntary to participate.

Data sources are existing databases (ObA2 database and the French National Health Data System - SNDS) to collect information about care pathways, patient characteristics and stroke characteristics and Ad hoc surveys to collect information about life pathways and post-stroke sequelae. The endpoints of the study are post-stroke activity limitations evaluated by the modified Rankin score, other post-stroke sequelae (Cognitive disorders, anxio-depressive disorders, fatigue, restriction of participation) assessed by standardized and validated scales and Clusters of patients responding to pathways with common or similar characteristics.;

**Discussion:**

By integrating a longitudinal dimension and relying on a large cohort, the project will make it possible to identify the sources of disturbances and the factors favorable to the outcome of the life pathways, important for the planning of the offer and the management of the public policies concerning stroke pathways.

**Trial registration:**

ClinicalTrials.gov ID: NCT03865173, March 6th, 2019.

## Background

### Stroke: a worldwide public health issue

Stroke is the leading cause of acquired physical disability in adults worldwide. It represents a real public health issue in terms of frequency, severity and cost.

Worldwide burden of stroke is huge, with 10.3 million new strokes per year and 113 million disability-adjusted life years (DALYs) per year [1, 2]. Stroke is the second cause of death and the third cause of disability adjusted life years worldwide [3]. Every year in France, about 110,000 patients present with a stroke, responsible for about 30,000 deaths, and 500,000 persons live with various level of disability following a stroke [4]. Many lifestyle risk factors (high blood pressure, diabetes, smoking, poor nutrition, sedentary lifestyle, etc.) [2, 5] and an aging population contribute to a steady increase in the incidence and prevalence of stroke.

Consequently, the socioeconomic impact of stroke is considerable. The annual cost of stroke in Europe is estimated to be €45 billion: €20 billion for direct care, €9 billion related to loss of productivity and €16 billion for informal care [6]. In France, in 2007, the economic burden of stroke amounted to about 8.6 billion euros [7]. This burden goes beyond the expenses incurred for the initial event. The expenditure of care during the first year represents a third of the direct costs [8]. The impact in terms of indirect costs, loss of income for active patients, time spent by family caregivers, accommodation of dependent people, adds to the burden of this pathology.

### Stroke: a severe disease requiring both urgent and chronic management

It is the very nature of the pathology, but also the consequences that stroke entails, which requires a management, both, extremely urgent and chronic. Indeed, stroke is a medical emergency that requires care in the shortest time. The advents of stroke units, of thrombolysis [9–11] and more recently of thrombectomy [12] have revolutionized acute stroke care, playing a decisive role in terms of vital and functional prognosis. However, the increase of stroke survivors related to major improvements in acute management and the aging of the population leading to an increase in the needs for post-stroke facilities [13, 14].

### Post-stroke sequelae

The consequences of stroke are potentially dramatic, with, on the one hand, high mortality, and on the other hand, for those who survive, short-term, medium-term and long-term sequelae requiring particularly heavy daily care. Sequelae spectrum is wide. They are physical (motor disorders, aphasia, sensory disorders), psycho-intellectual (cognition, depression), functional (activity limitation), or socio-professional (driving, loss of work, family difficulties) sequelae [15]. The World Health Organization’s International Classification of Functioning, Disability and Health (WHO-ICF) [16] gives a conceptual framework that can aid classification of the sequelae in three categories: disabilities (the direct loss of function), limitations of activities (formerly called disability) and participation restrictions (called handicap).

Sequelae can be measured by validated and standardized scales [17–23]. The most commonly used and specific ones are the modified Rankin score (mRS) [21] or the Barthel index (BI) [20].The mRS measures the degree of dependence in activities of daily living. This tool is widely used to measure the functional impact in clinical trials. The BI is an ordinal scale used to measure performance in activities of daily living.

### Predictive factors and outcome

Many studies have analyzed the stroke functional predictive factors [24, 25]. They can be sorted into three categories: variables related to the patient’s previous condition (age, sex, patient history, antecedents and autonomy before stroke), variables related to stroke (severity of hemiplegia, type of stroke - cerebral infarction or intracerebral hemorrhage) and finally variables related to the patient’s life pathways (speed of care in the acute phase, access to a stroke unit, early return home, social and familial environment). These factors interact with each other.

Among the variables related to the patient’s previous state, it is established that the autonomy, assessed by the modified Rankin score or the Barthel index, prior to stroke and at the inaugural event, is decisive in term of functional outcome.

Among the variables related to stroke, the initial severity of stroke, measured by the Institutes of Health Stroke Scale (NIHSS) [26], is one of the variables most strongly associated with the functional outcome.

With regard to the elements of the care pathway, several studies have showed that short and long-term outcomes after stroke are associated with better acute care, such as thrombolysis and stroke unit care, as well as risk factor management before and after stroke. As regards post-stroke pathways and outcome, only the role of rehabilitation treatment after a stroke [27–30] and the early supported discharge [31–34] have been shown as linked to functional outcomes. Reeducation must be initiated in stroke units, according to the patient needs, and continued and coordinated by a multidisciplinary team. However, no information exists on the functional role of further temporal and spatial elements of the downstream pathways following stroke.

### The stroke life pathways

The efforts of professionals and healthcare system regulators to improve the management of stroke patients first focused on the acute phase of the stroke management [35], and in particular hospital care within stroke units.

On the ground, however, multiple barriers impede the quality, fluidity and overall the efficiency of stroke care pathways. These obstacles mainly concern downstream support. Difficulties of referral to adapted structures after the acute episode are often encountered, with, as a consequence, number of patients admitted to rehabilitation remaining below public health objectives [36]. This represents a real loss of opportunity for some patients, impairing the speed of the implementation of rehabilitation which is a key element of functional outcome after a stroke. In addition, access to prevention, specialized care and medico-social structures is limited. The impact of these defects of care on functional outcomes have never been measured. Face to this lack of knowledge, it is difficult to define post stroke strategy to improve patient health. Furthermore, even more than the need for care, patient management after a stroke involves examining the situation of the person as a whole: his state of health, his autonomy in the daily life, his family and social environment and his resources. These different dimensions will have to evolve throughout pathway and will require a regular adjustment of the mods of accompanying.

Usually, three categories of management pathways for patients with chronic disease are identified: care pathways, health pathways and life pathways [37].

The care pathway is based on the right coordination of the various professional interventions related directly or indirectly to care. It integrates ambulatory and inpatient care (primary care and hospitalization, home hospitalization, follow-up and rehabilitation care, long-term care unit). The main objective of care coordination along the care pathway is to ensure that care is provided, to avoid duplication of unnecessary tests and to increase the safety and efficiency of care through reliable and shared information in real time [37].

Health pathways meet patient prevention, medico-social and social needs. These integrate the care pathways articulated with, on the one hand, preventive actions and, on the other hand, medico-social and social support, and the home return home (medico-social establishments, temporary accommodation and respite structures, home services, etc.) [37].

Finally, the life pathways refers to a global accompaniment of the person, based on the examination of his situation as a whole: personal life project, autonomy in daily life, state of health, family and social environment, resources, etc. These different dimensions are subject to change and require regular adjustment of the support arrangements implemented, involving multiple stakeholders and coordinated actions by the stakeholders [37, 38].

Pathways of stroke patients are not linear, but are divided into management sequences within health or medico-social facilities, evolving according to the complications and events directly or indirectly related to the stroke. Stroke patient care requires good organization and articulation of the different links in the care chain and the different care actors and, must consider the consequences of stroke on the person’s situation in his or her life context. Thus, the notion of “life pathways” is preferable to these of “care pathways” or “health pathways” [37, 38]. It is all the parameters integrated in the life pathways that make the post-stroke life pathways so complex that they are so far poorly known and poorly identified. Knowledge on their components, their typologies and on the functional role of their components is needed to construct a strategy taking into account post-stroke health as a whole.

### The French stroke management policy

In France, the 2010–2014 National Stroke Action Plan was launched to reduce the frequency and severity of stroke-related sequelae by improving the organization of regional care chain for stroke management. A reference stroke care pathway has been defined since the emergency to the relay with the medico-social actors and structures and / or the return home [39–41]. It defines the offer of care to be mobilized, for a standard stroke patient, as part of a linear pathway. The program of Health System Modernization [42] aims to develop and implement a patient integrated care pathway with a perspective of outcome.

Consequently, knowledge on the link between downstream pathway and functional outcomes will help constructing this program.

In the Aquitaine region, south western of France, the Aquitaine Stroke Observatory, ObA2, was set up by the regional health agency (ARS), as part of the regional plan for the fight against cardio-neurovascular diseases. This is a regional cohort of patients with a recent stroke, diagnosed and managed in the short-stay services of the hospitals in Aquitaine hosting more than 30 strokes per year. ObA2 objectives are: to 1) describe the management of stroke (practices, delays, referral of patients, etc.) prior to hospitalization, during hospitalization and in the post-hospital phase, 2) describe the population of stroke patients in socio-demographic and clinical terms, 3) monitor the population of these patients in terms of occurrence of complications during the stay, morbi-cardio-neuro-vascular mortality at 1 year and disability at 1 year. ObA2 is the only stroke cohort in France covering a whole region, allowing the inclusion of a large and heterogenic panel of stroke patients. The Observatory is a tool for improving practices and care pathways for patients with stroke. It is also used to develop research projects around stroke management. It is a tool to provide information to decision-makers to build a regional health strategy on the organization and care chain to help them structure the care pathways.

The PAPASéPA (Parcours des Patients victimes d’accident vasculaire cérébral et Séquelles Post-Accident vasculaire cérébral) project was built to address the lack of information on the components of the downstream life course and the link between these components and sequelae. In the ObA2 cohort dynamic, detailed data on the components of the life pathways, on the link between life pathway and sequelae could be used to better identify the needs to improve the health care system. We are in a global perspective of analysis of the life pathway of stroke patients, pre-hospital, hospital and post-hospital phases, and this for 1 year after acute care.

## Objectives

The main objective of the PAPASéPA project is to identify the life pathways components of stroke patients associated with the activity limitations measured by the Modified Ranking Score (mRS), at 3 months and 1 year after the acute episode.

The secondary objectives are to: 1) identify the life pathways components of stroke patients associated with other types of sequelae (cognitive disorders, anxio-depressive disorders, fatigue, restriction of participation) at 3 months and 1 year after the acute episode; 2) define a typology of the life pathways of stroke patients in Aquitaine, from acute care to 1 year of follow-up and 3) analyze the social and geographical inequalities in the management of stroke in Aquitaine.

## Methods/design

### Study design

The study design is an observational prospective cohort of stroke patients included in ObA2 with a patient follow up period for 1 year following stroke. Continuous data collection of care pathways will be carried out from stroke throughout the year of follow-up from existing databases (the ObA2 data base and the French National Health Data System (*Système National des Données de Santé -* SNDS); moreover, ad hoc collection of sequelae, pathways and socio-economic and environmental data is planned at three times (initial episode, at 3 months and 1 year after initial episode) (Fig. 1). The cohort is divided into three strata based on the severity of the patient’s initial clinical condition, as measured by the NIHSS score (≤6, [7–16], > 16) at the end of the hospital stay (Fig. 1).

**Fig. 1 Fig1:**
[figure not shown]
Structuring and design of the PAPASéPA project

Our analysis is based on the causal model linking life post-stroke pathway components and post stroke sequelae (Fig. 2). The adjustment factors are patients or stroke characteristics or stroke acute pathway elements/components identified in the literature as associated with stroke functional outcomes.

**Fig. 2 Fig2:**
[figure not shown]
Causal model of the link between downstream pathway and post-stroke sequelae

### Population and study sample

#### Study population

The study population involves patients diagnosed with a confirmed ischemic or hemorrhagic stroke included in the ObA2 cohort and managed in one of the 13 hospitals of the Aquitaine region, south Western France participating to Oba2. These 13 hospitals include 5 stroke units, 2 hospitals with neurologist and 6 hospitals without a neurologist.

#### Patient selection criteria

The inclusion criteria into the PAPASéPA cohort are: inclusion criteria to ObA2 (being over 18 years of age living in metropolitan France, suffering from a recent stroke whose diagnosis was confirmed by a neuro-vascular physician) and as additional criteria, Giving consent to participate to PAPASéPA).

Patients will be identified prospectively as they are included in ObA2. The inclusions will be carried out continuously and prospectively from the date of the beginning of inclusions (planned to be in september 2019) until the required number of subjects is obtained in each strata.

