### Data management and statistical analysis

#### Sample size selection

The primary endpoint is the mRS, measured at 3 months and 1 year after the stroke. Based on data from a pilot study, we assume a prevalence of independence of 51%, dependence of 30% and death of 19%. Several simulations were performed by varying the frequency of exposure to the risk factor studied (very rare to very common). By fixing the risk of first species at 5% and the power of the association test at 80%, to show an odds ratio of at least 2 (odds ratios to move to a higher class: independence to dependence or death, dependence on death), 368 patients should be included to cover a change in exposure to the risk factor studied, ranging from 20% (rare exposure) to 80% (frequent exposure).

The study is stratified on the NIHSS score assessed at inclusion (at the end of the hospital stay for acute episode management) in 3 categories (≤6, 7–16, > 16) and needs to include 368 patients per category of NIHSS or 1104 patients in total (software R v3.3.1).

To account for an estimated 5 to 10% of lost to follow-up, it is necessary to include 1210 patients.

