## Discussion

### Expected outcomes

By integrating a longitudinal dimension and relying on a large cohort, the new knowledge generated by this project will make it possible to identify the barriers and the factors favorable to the outcome of the life pathways, i.e.: 1) information on the elements of the pathway most closely associated with patient functional prognosis, 2) an accurate description of the life pathways, patients with stroke, by defining a typology of these pathways, information currently poorly known, especially on the downstream path, 3) very precise information on the frequency of post-stroke sequelae 3 months and 1 year after the stroke, information currently missing in France.

This information is important for the planning of the offer and thus to the shared and enlightened management of the public policies concerning stroke pathways. Thus, knowledge about the link between the life pathways and functional outcome will bring original information to reduce the impact of stroke by taking into account resources needed meeting the needs of patients and objective information on the inequalities of access to care and on the shortcomings of the healthcare offer.

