### Representativeness of cohort compared to stroke occurring in the Aquitaine region

A total of 13 health facilities are actively involved in the PAPASéPA project. They include all types of stroke facilities: 5 stroke units, 2 hospitals with neurologist and 6 hospitals without a neurologist. They are spread throughout the Aquitaine region (former Aquitaine region). Their annual stroke patients queue ranges from 70 to more than 1000. In 2016, these 13 centers cared for 5230 stroke patients, which represented 68% of strokes registered in the 2016 regional PMSI Aquitaine database. The comparison between the 2016 ObA2 cohort of these 13 centers and the 2016 PMSI stroke database showed similar age and type characteristics of stroke. Everything suggests that these 13 centers make it possible to constitute a cohort of stroke patients representative of the population of patients treated in Aquitaine for stroke.

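### Equal severity quotas filled by continuous inclusion give the three NIHSS strata different calendar windows, so pooled descriptive results mix severity with period

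*Protocol article*

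**What the plan says.** Under Patient selection criteria, patients are identified as they enter ObA2. Inclusion is continuous and prospective from a start planned for September 2019, "until the required number of subjects is obtained in each strata".

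Under Sample size selection, the strata are discharge NIHSS ≤6, 7–16 and >16. The study "needs to include 368 patients per category of NIHSS or 1104 patients in total". The allowance for losses follows: "To account for an estimated 5 to 10% of lost to follow-up, it is necessary to include 1210 patients".

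On patient flow, the Discussion section on representativeness states: "In 2016, these 13 centers cared for 5230 stroke patients". It concludes that these centres allow a cohort representative of stroke patients treated in Aquitaine.

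The Analysis plan derives a typology of pathways and compares social and geographical characteristics between pathway types; neither is said to be confined to a stratum. Expected outcomes promises "very precise information on the frequency of post-stroke sequelae 3 months and 1 year after the stroke".

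The article gives no discharge-NIHSS distribution, participation rate, recruitment duration or end date, and describes no sampling fraction.

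**The concern.** Equal quotas are a sensible way to secure enough severe patients. Combined with consecutive inclusion from a common start, however, they let the most frequent severity group fill first and close while the rarest group is still recruiting. Severity then becomes partly a marker of calendar period: mild patients come only from the opening part of recruitment, severe patients from all of it.

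This matters wherever the strata are put together. A typology built on the whole cohort, a comparison of social and geographical profiles between pathway types, and overall sequelae frequencies would combine severity groups seen under possibly different seasons and care offers. Reweighting the strata to their natural shares corrects the unequal sampling of severity, but it cannot supply mild patients for the months in which none were enrolled.

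**Working it through.** **1. The plan's own number.** Inputs from Sample size selection: odds ratio 2, power 80%, α 5% (taken as two-sided), outcome distribution 51/30/19%, exposure prevalence f = 20% or 80%. Whitehead's proportional-odds formula:

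N = 3(z₀.₉₇₅ + z₀.₈₀)² / [f(1−f)(ln 2)²(1 − Σp³)]

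Σp³ = 0.51³ + 0.30³ + 0.19³ = 0.1665, so N = 3 × 7.849 / (0.16 × 0.4805 × 0.8335) = 367.5, i.e. 368. The stated figure reproduces. Three strata give 1104. The figure of 1210 corresponds to 1 − 1104/1210 = 8.8% loss, inside the stated 5–10%. Per stratum, 1210/3 = 403.3.

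**2. Does each stratum close at its quota?** The wording could also mean that all strata stay open until the last one fills. The totals speak against that. With illustrative shares of 70% mild and 10% severe and equal participation, 403 severe patients would arrive alongside 403 × 7 ≈ 2,800 mild ones, far beyond 1210.

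**3. Ratio of windows.** With annual flow F, stratum share s and participation c, time to fill a quota q is q/(F·s·c). For equal q and c,

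mild window / severe window = s(severe) / s(mild).

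Flow and participation cancel. The shares are assumptions, because the article gives none: mild 60–80%, severe 3–15%.

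- Lowest: 0.03/0.80 = 3.75%
- Highest: 0.15/0.60 = 25%
- Equal windows only if each share is one third

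**4. Absolute durations.** Months = 404 / (5230 × s × c) × 12, with the 2016 flow of 5230 and the quota rounded up to 404:

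| Stratum and assumed share | c = 100% | c = 50% | c = 20% |
|---|---|---|---|
| ≤6, 80% | 1.2 | 2.3 | 5.8 |
| ≤6, 60% | 1.5 | 3.1 | 7.7 |
| >16, 15% | 6.2 | 12.4 | 30.9 |
| >16, 10% | 9.3 | 18.5 | 46.3 |
| >16, 3% | 30.9 | 61.8 | 154.5 |

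The durations vary widely with the assumptions. The severe stratum needs a year or more only if share × participation is at most 404/5230 = 7.7% (7.0% with a quota of 368).

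**5. What overlap remains.** With steady arrivals, the number of severe patients enrolled while the mild stratum is still open is 403 × 0.0375 ≈ 15 to 403 × 0.25 ≈ 101. Outside that overlap, adjustment for date would have to extrapolate for mild patients.

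**The case against.** Much of the case on the other side stands.

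- **Durations.** A reader might infer that mild patients come from a few weeks and severe patients from a year or more. The article does not support this as fact: it would need stratum shares and participation that are not given, and the table above shows how far the answer moves. Only the inverse relation between window and arrival rate follows from the text.
- **Nurse capacity.** Research nurses visit the site at the end of each stay, and only three people measure the mRS. An 80% share at full participation means 5230 × 0.80/12 ≈ 349 mild inclusions a month. If capacity binds, the mild window lengthens and the contrast may shrink.
- **Main objective.** A reader might infer that the primary result is biased. The sample size is set per stratum, and within a stratum a timing difference between strata cannot confound an association with the mRS. A direct comparison of sequelae between strata is not among the stated analyses either.
- **Late-opening centres.** A reader might suppose that such centres would contribute no mild patients. No staggered opening is described.
- **Size of bias.** Nothing in the article shows how far pathways change with season or period, so the bias itself cannot be quantified. Every patient is followed for a year, and onset and admission dates are collected, so adjustment for date or restriction to the overlap is possible and may be planned in the SAP. Its absence here is no finding. Neither remedy, however, observes mild patients after their stratum has closed.

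Pacing rules might also sit in the full protocol. The point therefore rests on the recruitment rule that the article does state, not on what it omits.

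**Conclusion.** The point holds in a limited form. The stated rule and the equal quotas make calendar window depend on severity unless the three strata arrive at equal rates. Under assumed shares of 60–80% mild and 3–15% severe, equal participation and no capacity limit, the mild window covers about 4–25% of the severe one. The consequence is confined to outputs that pool strata or describe the region: the typology, the social and geographical comparison, the sequelae frequencies and the claim of representativeness. That claim rests on comparing the 2016 ObA2 cohort of these centres with the regional hospital database, which says nothing about when each stratum enrols. The sample size and within-stratum associations are unaffected. This is an inexpensive design improvement that should be made; it does not invalidate the study.

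**What to change.** In Patient selection criteria, replace consecutive filling of the faster strata by systematic sampling. In each centre, approach every k-th consecutive ObA2 patient with discharge NIHSS ≤6, use a smaller k for 7–16, and approach all patients with NIHSS >16. Set k from existing ObA2 discharge-NIHSS counts and update it during recruitment so that the three strata fill over the same period. For illustration, shares of 70/20/10% with equal participation would give k = 7 for mild and k = 2 for intermediate patients. State the expected shares and recruitment duration beside the rule.

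Cost: no additional patients or staff, since the slowest stratum already determines when the study ends. The mild stratum and its one-year follow-up finish later, and a poorly chosen k would under- or over-fill a stratum until corrected. The extraction period for the national health data (Data sources: September 2019 to August 2020) must also be reconciled with the inclusion period plus one year of follow-up. It spans only twelve months, so it cannot cover a full year for anyone included after its start, and later mild inclusions would put more follow-up outside it.
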